## Abstract

**Background:**

Post-term pregnancy is associated with an increased risk of maternal complications, respiratory distress and trauma to the neonate. Amniotic membrane sweeping has been recommended as a simple procedure to promote the spontaneous onset of labour. However, despite its widespread use, there is an absence of evidence on (a) its effectiveness and (b) its optimal timing and frequency. The primary aim of the MILO Study is to inform the optimal design of a future definitive randomised trial to evaluate the effectiveness (including optimal timing and frequency) of membrane sweeping to prevent post-term pregnancy. We will also assess the acceptability and feasibility of the proposed trial interventions to clinicians and women (through focus group interviews).

**Methods/design:**

Multicentre, pragmatic, parallel-group, pilot randomised controlled trial with an embedded factorial design. Pregnant women with a live, singleton foetus ≥ 38 weeks gestation; cephalic presentation; longitudinal lie; intact membranes; English speaking and ≥ 18 years of age will be randomised in a 2:1 ratio to membrane sweep versus no membrane sweep. Women allocated randomly to a sweep will then be randomised further (factorial component) to early (from 39 weeks) versus late (from 40 weeks) sweep commencement and a single versus weekly sweep. The proposed feasibility study consists of four work packages, i.e. (1) a multicentre, pilot randomised trial; (2) a health economic analysis; (3) a qualitative study; and (4) a study within the host trial (a SWAT). Outcomes to be collected include recruitment and retention rates, compliance with protocol, randomisation and allocation processes, attrition rates and cost-effectiveness. Focus groups will be held with women and clinicians to explore the acceptability and feasibility of the proposed intervention, study procedures and perceived barriers and enablers to recruitment.

**Discussion:**

The primary aim of the MILO Study is to inform the optimal design of a future definitive randomised trial to evaluate the effectiveness (including optimal timing and frequency) of membrane sweeping to prevent post-term pregnancy. Results will inform whether and how the design of the definitive trial as originally envisaged should be delivered or adapted.

**Trial registration:**

ClinicalTrials.gov NCT04307199. Registered on 12 March 2020

**Supplementary Information:**

The online version contains supplementary material available at 10.1186/s13063-021-05043-9.

## Background

Labour and childbirth are physiological processes, and for the majority of women, the onset of labour is spontaneous. However, some women will have an induction of labour. Induction of labour is the process of artificially stimulating uterine contractions to initiate the onset of labour. Approximately one in four pregnancies in the developed world will end with an induction of labour [1, 2].

Current World Health Organization guidelines note that induction of labour, as with any intervention, carries risks and advise that induction of labour is not recommended for women with uncomplicated pregnancies less than 41 weeks gestation [2]. Conversely, in response to the findings of recent studies which report that elective pharmacological induction of labour results in a lower risk of caesarean section than expectant management, the American College of Obstetricians and Gynecologists has amended their guidance to support elective induction of labour of low-risk women, having their first baby, at 39 weeks gestation [3–5]. Medical indications for induction of labour include preterm premature rupture of membranes (PPROM), intrauterine growth restriction, hypertensive disorders of pregnancy, intrauterine foetal death and post-term pregnancies [6]. Of these, post-term pregnancy is the most common [7, 8].

A pregnancy is considered to have reached full term at 37 completed week’s gestation; however, some pregnancies will continue past 41 weeks’ completed gestation and are then considered ‘post-term’ [9]. The rates of post-term pregnancy, defined as a pregnancy that has reached 42 weeks gestation from the last menstrual period (LMP), vary worldwide (0.2% in Belgium, 5.8% in the USA, 7% in Sweden) [9–12]. Birth post 42 weeks’ gestation carries an increased risk for the neonate including increased risk of meconium aspiration, neonatal acidaemia, low Apgar scores, macrosomia and neonatal death [13, 14]. The incidence of maternal complications such as severe perineal injury (third- and fourth-degree perineal lacerations) related to macrosomia, post-partum haemorrhage, chorioamnionitis and endomyometritis is increased post-term [15].

Labour may be induced using pharmacological, surgical and mechanical methods.
Pharmacological methods include the use of prostaglandins, such as dinoprostone administered either vaginally or intracervically; misoprostol administered orally, vaginally or intracervical; and oxytocin administered intravenously [16]. Pharmacological methods of induction of labour are not suitable for all women [17]. Reduced levels of prostaglandins are indicated in women with high parity, and the use of prostaglandins is contraindicated in cases of women with a previous caesarean section [17]. Pharmacological induction of labour increases the risk of uterine hyperstimulation [17].Surgically, labour may be induced using procedures including the deliberate rupturing of the amniotic membranes known as amniotomy [18]. Amniotomy carries the risk of umbilical cord prolapse and is contraindicated when the presenting part of the foetus is not engaged in the pelvis and in women with a history of placenta praevia and vasa praevia. It also increases the risk of infection for the mother and foetus and is contraindicated in HIV-positive women [19, 20].Mechanical methods of induction of labour are used to ripen and dilate the cervix encouraging the spontaneous onset of labour through manual manipulation of the cervix [21]. Mechanical methods include the use of an intracervical Foley catheter and amniotic membrane sweeping, also referred to as ‘stripping’ or ‘stretch and sweep’ of the membranes.

This study seeks to evaluate the role of membrane sweeping.

### Description of the intervention

An amniotic membrane sweep is performed with consent during a vaginal examination. It involves the clinician inserting one or two fingers into the woman’s cervix and detaching the inferior pole of the membranes from the lower uterine segment in a circular motion [22]. Membrane sweeping is a simple procedure and may be used independently or in combination with other means of induction and can be repeated multiple times.

### How the intervention might work

Amniotic membrane sweeping is used to promote the onset of labour by releasing localised prostaglandins F2α, phospholipase A2 and cytokines from the intrauterine tissues [23]. These hormones act on the cervix to augment cervical ripening potentially instigating uterine contractions. The manual stretching of the cervix may help to initiate the Ferguson reflex by releasing oxytocin thereby increasing uterine activity [23]. The aim of amniotic membrane sweeping is to soften and ripen the cervix, increasing cervical favourability and stimulate spontaneous uterine contractions potentially leading to the onset of labour and avoidance of a formal induction of labour.

### Why is this research needed?

Post-term pregnancy is by far the most common reason for induction of labour, and membrane sweeping offers a potentially low-risk method to reduce this. Membrane sweeping is a technically simple intervention and may be performed by clinicians in a community or clinical settings potentially providing significant reductions in cost [17, 24]. Recent studies have supported elective pharmacological induction of labour to lower the risk of caesarean section. However, these studies compared induction of labour to expectant management only, with none evaluating the potential effects of membrane sweeping on the process [4, 5]. Our Cochrane systematic review found that, when compared to expectant management, membrane sweeping is potentially associated with an increased rate of spontaneous onset of labour (average RR 1.21, 95% CI 1.08 to 1.34) and a lower risk of formal induction of labour (average RR = 0.73. 95% CI 0.56–0.94) when compared with expectant management [25]. It is not associated with increased rates of infection or premature rupture of the membranes and has the advantage that it may be used independently or in combination with other means of induction and can be repeated multiple times.

Guidelines by bodies including NICE [17], the Society of Obstetricians and Gynaecologists of Canada [26] and the Department of Health, South Australia [27], state that women should be offered the option of membrane sweeping at or near term. However, the optimum gestation to perform a membrane sweep to promote cervical ripening is unknown. Further, there has been a little direct comparison of the effect of multiple membrane sweeps versus a single membrane sweep to promote spontaneous labour. Internationally, guidelines have identified the need for research to clarify these uncertainties [17, 28]. In addition, our recent Cochrane systematic review found a lack of data on the optimal timing and frequency of membrane sweeping and recommended future research in this space [25]. A cost-effectiveness analysis, including an antenatal, intrapartum, postnatal and neonatal cost analysis, comparing membrane sweeping with expectant management and other methods of labour induction has not been carried out. In a time where health care providers are weighing cost-effectiveness with quality of care, this would provide invaluable data to inform health policy and is an important gap identified in our Cochrane Systematic review [25].

Clinician’s views and acceptability of membrane sweeping have been significantly under-represented in research. In addition, few studies explored women’s views of membrane sweeping. Further research to explore women’s and clinician’s experiences and views of membrane sweeping as a method of induction of labour is needed to support the clinical application of this intervention and to inform future definitive evaluations.

## Methods/design

### Trial aim and objective

The primary objective of the MILO Study is to assess the feasibility of conducting a definitive randomised controlled trial to examine the effectiveness, and optimal intensity (timing and frequency), of membrane sweeping to prevent post-term pregnancy. The study consists of four work packages.
*WP1*: *a pilot randomised trial* assessing the feasibility of conducting a definitive trial to evaluate how often and the best time to perform a membrane sweep*WP2*: *health economic analysis* assessing the feasibility of conducting a trial-based economic evaluation to examine the cost-effectiveness of membrane sweeping*WP3*: *a qualitative study* exploring the acceptability of the trial for women and clinicians*WP4*: *a study within a trial (SWAT)* assessing if the point at which women are invited to take part in the trial (i.e. when should women be asked?) affects the number of women recruited to and retained in the trial

## Methods

The proposed feasibility study consists of four work packages:

### Work package 1: Pilot randomised trial

#### Methods/design

We will use a multicentre, pragmatic, parallel-group pilot randomised controlled trial with an embedded 2 × 2 factorial design (Fig. 1). This allows an examination of the feasibility of a staged ‘gated’ approach to trial analysis in a future definitive trial. For example, it allows us to evaluate the feasibility of a future trial to answer the primary question ‘is membrane sweeping effective in preventing post-term pregnancy?’ and also address the effectiveness of different timings and frequency of membrane sweeping. The advantage of using a factorial design in the MILO Study is that we can assess two individual questions simultaneously in the same population.

**Fig. 1 Fig1:**
[figure not shown]
Study design

By utilising resources dynamically, we ensure a more efficient use of resources including sample size and time [29]. A factorial design requires a smaller sample size when compared to running two separate parallel trials resulting in reduced running and management costs and shorter time frame. The protocol has been prepared in line with the Standard Protocol Items: Recommendations for Interventional Trials (SPIRIT) guidelines (Additional file 1) [30].

#### Setting

The MILO Study will be set in the antenatal outpatient departments in two Irish maternity hospitals.

#### Participants

##### Inclusion and exclusion criteria

Pregnant women carrying a live singleton foetus ≥ 38 weeks completed gestation (gestational age will be calculated from the first day of the last menstrual period and an ultrasound examination carried out in the 2nd trimester) will be eligible. The lie must be longitudinal, presentation cephalic and amniotic membranes intact. Women must be ≥ 18 years of age on enrolment. Women will need to be able to communicate in English and give written informed consent. Women with any contraindications to a vaginal examination or vaginal birth (i.e. placenta praevia, vasa praevia, antepartum haemorrhage or undiagnosed vaginal bleeding, malpresentation, i.e. transverse lie, Herpes simplex virus with active genital lesions or prodromal symptoms) will be excluded from the MILO Study.

#### Recruitment

Written trial information will be offered to women potentially eligible for participation at 35–36 + 6 week’s gestation or at 37–38 + 6 week’s gestation, depending on SWAT randomisation (see below), during routine antenatal appointments in each site. Clinicians and/or research midwife at participating antenatal clinics will identify women who are potentially eligible to participate in the study. Women will be given an information pack that will include a letter introducing the trial and a participant information leaflet, which will inform potential participants of the background and purpose of the study, risks and benefits of participation, what participants are being asked to do, their right to withdraw and offer to answer any questions they have relating to the study. This will be followed up at the 39-week antenatal visit when the researcher will invite eligible women to participate.

#### Obtaining informed consent

At the 39-week antenatal visit, the potential for inclusion to the trial will be checked by the attending midwife and/or research midwife. The trial will be explained, and questions potential participants might have will be answered. Eligible women will be asked to participate at this time, and written informed consent will be obtained from women agreeing to participate.

#### Randomisation and allocation concealment

Randomisation to intervention and control will be at the level of the individual, i.e. individual randomisation, stratified by parity and centre. Randomisation is on 2:1 ratio; that is, for every two women randomised to the intervention arm (sweeping intervention), one will be randomised to the control arm (usual care). Women in the intervention group will further be randomised in a ratio of 1:1 to the factorial design. The random allocation sequence will be generated using a computer-generated random number list. Random permuted blocks of sizes 6 and 12 will be used to determine the group allocation. Randomisation will be stratified by (a) parity to ensure appropriate representation of primiparous and multiparous women to each group and (b) centre using a separate block randomisation list for each of the two centres. Block sizes will be concealed until completion of the trial.

To ensure concealment of allocation, randomisation will be done electronically using web-based random allocation based on random sequence generation detailed above. The enrolling midwife will log stratification factors with the randomisation service through a web interface after which he/she will be informed of the allocation (usual care or group allocation in the 2 × 2 factorial design) and the unique study ID number, which will be documented on the consent form.

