#### Blinding

Clinicians performing a membrane sweep cannot be blinded, and it is not feasible to genuinely blind membrane sweeping for women. Therefore, neither clinicians administering the intervention nor women will be blinded to the group assignment. Data will be reviewed by two assessors blinded to the group allocation.

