## Data Availability

The MILO Study has not yet begun recruiting. All data and materials will be available from the corresponding author on reasonable request.

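### The block sizes that the protocol promises to conceal are printed in the same paragraph, so someone tracking a list could know a few allocations with certainty

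*Protocol article*

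**What the plan says.** Under Randomisation and allocation concealment, the protocol article sets a 2:1 allocation of sweep to usual care. It then adds: "Women in the intervention group will further be randomised in a ratio of 1:1 to the factorial design". On blocking it states: "Random permuted blocks of sizes 6 and 12 will be used to determine the group allocation". Stratification is by parity and by "centre using a separate block randomisation list for each of the two centres". The paragraph ends: "Block sizes will be concealed until completion of the trial".

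Allocation is web-based. The enrolling midwife enters the stratification factors, "after which he/she will be informed of the allocation (usual care or group allocation in the 2 × 2 factorial design"). Under Blinding, "neither clinicians administering the intervention nor women will be blinded to the group assignment".

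On timing, Data Availability says "The MILO Study has not yet begun recruiting". Trial status gives a planned start in February 2021 and a protocol version dated 5 January 2021.

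**The concern.** Block sizes are withheld so that staff who can see past allocations cannot work out when a block is nearly used up. Central web allocation hides the list but does not prevent inference from what has already been allocated. Hiding the sizes is the safeguard against that, and the article gives them away.

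The other conditions for inference are present: open allocation, results reported down to the factorial group, and short lists because of stratification. A member of staff who knows that the next woman will be, say, a control could time or steer the approach to her. That would threaten group comparability.

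This matters even in a pilot. Recruitment and evaluation of the randomisation process are primary feasibility outcomes, and recruitment of at least 30% of eligible women is a progression criterion. The embedded study within a trial also lists evaluation of randomisation, allocation and concealment among its primary outcomes. If the same scheme passed into the definitive trial, a confirmatory comparison would be exposed.

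**Working it through.** **The contradiction.** One sentence gives the sizes as 6 and 12, and a later sentence in the same paragraph says they stay hidden until the trial is complete. Both cannot hold once the article is public. The article gives no predictability figure to reproduce, so the size of the effect has to be estimated.

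**Inputs from the protocol article**
- Ratio 2:1, so a block of 6 holds 4 sweep and 2 control, and a block of 12 holds 8 and 4.
- 2 centres × 2 parity levels = 4 lists.
- 132 women in all (Sample size for pilot trial).

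**Assumptions**
- Parity splits evenly, so 132 / 4 = 33 women per list.
- Each block's size is drawn at random, with size 12 having probability 1/2 or 1/3 (the mix is not stated).
- In the cell-tracking case, A–D are balanced within blocks: one each plus two controls per 6.
- The observer sees every earlier allocation on the list.

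**How certainty arises.** Suppose the first six women on a list are three controls and three sweeps. A block of 6 holds only two controls, so this block must be a 12. The six places left hold 4 − 3 = 1 control and 8 − 3 = 5 sweeps. Once that control appears, every later woman in the block is certain to be allocated a sweep. An observer not told the sizes would have to allow for 18 (12 sweep, 6 control) or more, and could not be certain.

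**Simulation.** The observer updates by Bayes' rule over the possible block sizes and remaining counts, then guesses the most probable allocation.

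Reference with no tracking: always guessing sweep is right 4/6 = 67% of the time. Always guessing control, the largest single group, names the exact group 2/6 = 33% of the time.

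| Observer tracking a list of 33 | Exact group right | Sweep v control right | Sweep v control certain | Lists with at least one certain |
|---|---|---|---|---|
| Knows 6/12, tracks arm only, P(12) = 1/2 | – | 71.5% | 5.7% | 66% |
| Knows 6/12, tracks arm only, P(12) = 1/3 | – | 72.0% | 4.2% | 52% |
| Knows 6/12, tracks A–D, P(12) = 1/2 | 44.6% | 71.7% | 8.4% | 89% |
| Knows 6/12, tracks A–D, P(12) = 1/3 | 45.3% | 72.4% | 6.3% | 76% |
| Assumes only multiples of 6 up to 24, tracks A–D, true sizes 6/12 with P(12) = 1/2 | 44.4% | 71.8% | 0% | 0% |

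A repeat run of the third row gave 8.7% certain, so the range is about 4% to 9%. In women, 0.04 × 132 = 5.3 and 0.09 × 132 = 11.9, that is, about 5 to 12.

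**What disclosure adds.** The fair comparison is the third row with the last, because both observers track the list and only one knows the sizes. Average accuracy is the same (71.7% and 71.8%; 44.6% and 44.4%). Certain allocations go from none to about 8%. Disclosure therefore creates the certain allocations but not the average gain over 67% or 33%.

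**The case against.** The strongest reply is that the practical risk is small.

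- **The list is still hidden.** Allocation is released by a web service only after the woman's factors are logged, and neither the list nor the order of block sizes is disclosed. This stands. It is therefore too strong to infer that allocation concealment as a whole has failed; one supporting safeguard has.
- **The average gain is not due to disclosure.** A reader might charge the whole rise, from 67% to 72% for sweep versus control or from 33% to about 45% for the exact group, to the printed sizes. The last row of the table shows otherwise. This stands in full.
- **Nobody need see a whole list.** A reader might infer that one midwife sees every earlier allocation in her stratum. The article says only that the enrolling midwife is told the allocation of the woman just logged. Obtaining informed consent and Clinician training involve several kinds of staff. Several enrolling staff per site would dilute the risk, so the percentages are upper bounds.
- **The publication date is not shown.** A reader might conclude that the article was already public before recruitment opened. The text shows only that it was written before then.
- **Balance of A–D within blocks is not stated.** If blocks balance only sweep against control, the range is 4–6%.
- **There is little room to delay.** Consent is taken at the 39-week visit, randomisation comes immediately before the intervention starts, and two of the four sweep groups begin at 39 weeks. No formal hypothesis testing is planned. Both points limit the harm. Neither removes the contradiction, or its bearing on a pilot that sets out to evaluate its own randomisation.

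**Conclusion.** The contradiction is real and lies within one paragraph. Its attributable effect is limited: up to about 4–9% of allocations (about 5–12 of 132) become certain to someone who knows the sizes and tracks a list, against essentially none if the sizes were hidden. This rests on about 33 women per list, an assumed mix of block sizes and complete tracking. The upper end also needs A–D balanced within blocks. The documents do not support a claim that disclosure raises average predictability, that any one person can follow a whole list, or that the recruitment results would be distorted by a known amount. The correction is still worth making before recruitment opens, because it is cheap and the pilot is meant to test the definitive trial's procedures.

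**What to change.** Before the first randomisation, have the randomisation service generate the four lists with different, randomly varying block sizes known only to that service. Deleting the printed sizes is not enough, because 6 and 12 are already disclosed. Replace the two block-size sentences with wording such as *randomly varying block sizes, not disclosed to sites*, and keep the sizes out of training material. Do the same for the definitive trial.

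Preferably include larger blocks. If A–D are balanced within blocks, any size must still be a multiple of 6, so hiding the sizes removes certainty but leaves much of the average predictability. In an example with hidden sizes of 12 and 18, sweep versus control is guessed correctly about 70% of the time and the exact group about 41%.

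The cost is one regenerated set of lists and a two-sentence amendment. Sample size, visits and analysis do not change. The small downside is slightly looser balance within short strata, since a list of about 33 may end part-way through a larger block.
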